### Study outcome measures

#### Primary outcome measure

The primary outcome measure is d_3_mft at 2 years of follow up compared to the d_3_mft at baseline (d_3_mft is dental decay as measured by the number of: teeth affected by decay into the dentine; missing teeth; and filled teeth).

#### Secondary outcome measures

##### d_3_mfs

The d_3_mfs scale is a count of affected surfaces rather than teeth. The d_3_mft and d_3_mfs measures will be obtained through detailed dental examinations which follow the protocol adopted for the NHS Scotland National Dental Inspection Programme (NDIP), which involve P1 and P7 children. The examinations will be conducted by NDIP dentists following a training and calibration exercise. In addition, dental decay outcomes will be assessed by deprivation SIMD strata.

##### Child records of dental treatment and attendance

With parental informed consent, the children’s records of dental treatment and attendance held by Information and Statistics Division, NHS Scotland, will be examined to establish a profile of contact with and treatment by dental services in the two arms of the study.

##### Quality of life

In addition to clinical data, the trial will also collect data on children’s’ general and oral health and quality of life using a battery of questionnaires, distributed at three points in the trial: at baseline, 12 months and 24 months. Parents/guardians of participants will be asked to complete:The Child Health Utility 9D for under 5-year-old children (CHU9D) – parental proxy questionnaire ([23, 27], and [name], personal communication, May-June 2014) (Additional file 2);The Paediatric Quality of Life Inventory (PedsQL) – the PedsQL 4.0 Generic Core Scale Parental Report for Toddlers (ages 2–4 years) [29, 22, 30] (Additional file 3);The Scale of Oral Health Outcomes for 5-year-old children (SOHO-5), parental proxy questionnaire ([25, 26], and [name] personal communication, May 2014) (Additional file 4).

##### Health and dental care services resource use

A questionnaire (Additional file 5) designed to elicit information on uptake of health and dental care services and medication use by the child within the past 12 months will also be distributed in the quality of life questionnaire pack at each of the three rounds.

##### Subjective global transition judgement question

Parents/guardians will be asked to answer two subjective global transition judgement questions in the questionnaire packs (Additional file 6) distributed at 12 and 24 months. This will be used as a method to assess the QoL instruments’ responsiveness to change [1]. The questionnaire packs will be distributed to the families via the nurseries or posted to the family’s home address.

### Follow-up procedures parental questionnaire survey

A number of well-established techniques to enhance response rates will be used. These are:the cover page (Additional file 7) for the questionnaire pack sent at baseline offer parents/guardians the opportunity to enter a prize draw for an iPad. This offer will be repeated for each of the two subsequent rounds of the survey;there will be an unconditional incentive in the form of a Childsmile branded pen and a page of Childsmile stickers (for the child) contained within the questionnaire pack;a sense of participation in the study will be encouraged by the distribution of Christmas cards and/or a study newsletter updating on the progress of the study, and encouraging completion of the parental questionnaires;parents who had previously provided a mobile telephone number will receive a text reminder if they have not returned the questionnaires within 1 week;at the end of the second week a second copy of the questionnaire pack will be mailed to any non-responders directly to their home address or distributed via the child’s nursery;at the end of the third week the non-responder parent will be contacted by telephone to remind them to complete the questionnaires.

The techniques described above have been adapted from those used by the Seal or Varnish trial [5] run by South East Wales Trials Unit/Cardiff University.

### Data linkage

In order to be able to link the trial outcome measures by child with the children’s records of dental treatment and attendance held by Information and Statistics Division, NHS Scotland, we will request, at the beginning of the trial, a full home address from the parents/guardians of trial participants.

### Laboratory tests

None.

### Assessment of safety

As part of the recruitment process, parents will be asked about contraindications for fluoride varnish. The most common of these are a history of hospitalisation for bronchial asthma or allergic reactions. Other contraindications are: hypersensitivity to colophony and/or any other fluoride varnish constituents.

Temporary conditions such as ulcerative gingivitis and stomatitis will be checked on the day of the application, following the normal Childsmile procedure detailed below. This procedure is within the clinical remit of the Extended Duty Dental Nurses employed to deliver the Childsmile Fluoride Varnish programme, and includes the following steps:check the skin of the face and around the mouth for abnormalities (spots, inflammation, swelling etc.)check the lips for lesions/infections.check the inner cheeks and the insides of the lipscheck the upper and lower surfaces of the tongue.Children showing obvious signs of systemic illness (e.g., colds, flu) or any abnormality of the face, lips or soft tissues of the mouth should be excluded on the day from Fluoride Varnish application.The teeth and gums should be checked for signs of infection in a systematic order.

#### Adverse reaction reporting

If there are any immediate adverse reactions to the Fluoride Varnish (e.g., mucositis, allergy etc.) the product will be removed by toothbrushing and rinsing, following the Childsmile local protocol. The possible adverse reaction may be noticed immediately by the dental team or later by the teachers or parents. Any such reports will be transmitted by the Childsmile study team to the family dentist, the Childsmile coordinator and the local Principal Investigator. This information will be updated on the child’s notes accordingly.

### Investigational drug information

Children who are eligible for the study will be randomised to receive fluoride varnish treatment as Duraphat® Dental Suspension. Further details of treatment schedules are given below.

#### Treatment schedule

At each treatment, a total volume of 0.25 ml of Duraphat® Dental Suspension will be applied to the teeth in children randomised to the intervention treatment. Each 1 ml of Duraphat® Dental Suspension contains 50 mg sodium fluoride which is equivalent to 22.6 mg of fluoride. The protocol treatments will be applied at six monthly intervals for 18 months i.e., baseline, and at 6 months, 12 months and finally 18 months post-baseline (all timings +/- 3 months).

#### Rationale for chosen treatment schedule

The treatment schedule chosen is in line with current practice guidelines (Guideline 83. [20]) and the approved summary of product characteristics.

A 0.25 ml dose of Duraphat® dental suspension contains 5.6 mg of fluoride. The toxic dose of fluoride ingestion is estimated at 75 mg for an average sized 3 year old weighing 15 kg, so such a child would have to swallow 2 whole cartridges to ingest a toxic amount. Any child suspected of swallowing excessive levels should be given lots of milk to drink and transferred to the local A&E Department for a gastric lavage [9].

A child in the study may receive fluoride varnish up to a maximum of four times a year (twice in study applications and twice from their own dentist if their practice is participating in their Childsmile Practice programme.) This represents a total dose of 22.6 mg of fluoride spread over four applications per year, and is well within the Scottish Dental Clinical Effectiveness Programme’s (SDCEP) clinical guidelines [15] and is within the safe limits for both acute toxicity levels and chronic ingestion resulting in fluorosis. Even if the child were to receive two doses on the same day, there would be no risk of toxicity as two doses would give the child 11.3 mg of available fluoride, still well within the dose safety margin. There would also be very little chance of fluorosis as, after the age of 4 years, most of the adult teeth have already calcified. A dose of 25 mg four times per year is within the SDCEP’s clinical guidelines [15].

#### Investigational product administration

The procedure will follow the standard practice of the Childsmile Nursery programme [13] and will be detailed in full in the study management procedures. An outline of the procedure is given below.

##### Safety assessment prior to treatment

A safety assessment procedure will be carried out by the team prior to each treatment application. The safety assessment reduces the possibility of children with oral/facial infections being included. Any child with any abnormality of the lips, face or soft tissues of the mouth will be excluded from fluoride varnish treatment scheduled for that day. Children who are showing obvious signs of systemic illness e.g., colds, 'flu, chicken pox etc. will also be excluded on that day. An extra-oral and intra-oral assessment will be conducted. Thereafter, the teeth and gums will be checked for signs of infection starting with the upper right and then moving to the upper left, lower right and finally the lower left. If the risk assessment is negative the fluoride varnish will be applied. Children who have signs of decay will still have the fluoride varnish applied as it may help protect from further decay and it will familiarise the child to dental treatment.

##### Treatment

Starting with the upper right side, the cheek will be retracted with a finger or mirror and the canine and molars dried with a cotton roll. With the cotton roll in place, a small amount of Fluoride Varnish will be applied to the contact points of the canine and molars and to the occlusal surfaces of the molars. The same procedure will be repeated for the upper left quadrant and lower quadrants. The remaining varnish will be applied to the labial surfaces of the canines and incisors. The dental nurse will then complete a check to ensure that all equipment is removed from the mouth and disposed of in line with current procedures.

If the child becomes upset or protests during any part of the procedure, then the procedure will be halted, and only resumed if the child can be reassured and put at ease. If any immediate adverse reaction is suspected, the varnish can be easily removed by toothbrushing, rinsing and spitting. Children who miss one or more of the treatments are still eligible to receive any remaining treatments. Children with an incomplete record of treatments or contacts will be retained in the study, even if all treatments and contacts are missed.

### Study supplies

#### Supply of study treatment

Commercially available UK supplies of Duraphat® Dental Suspension will be used in the study. All supplies for use in the study will be sourced from via normal NHS supply mechanisms. There will be no study specific supplies.

Duraphat® Dental Suspension is presented in 10 ml aluminium tubes. As per current standard practice, each tube will be used for multiple participants. In order to prevent any potential cross-contamination, a single 0.25 ml dose will be measured out by the dental nurse prior to the start of the procedure and the resealed tube will be returned to either a locked cupboard or transport box. Any Duraphat® Dental Suspension which remains at the end of 7 days will not be used for study purposes.

#### Labelling of study treatment

There will be no study specific labelling. All supplies to be used in the study will be UK licensed stock prescribed by a dentist and labelled in accordance with current regulatory requirements for Prescription Only Medicines including instructions for use, expiry date and batch details. The investigational product will be used in accordance with the Summary of Product Characteristics for multiple study participants within a clinic type setting under a dentist prescription and will not be dispensed for use by an individual participant. To ensure traceability, the batch number will be recorded at each participant treatment.

#### Storage of study treatments

As this is a phase IV study of an established treatment intervention conducted as part of a national programme, continuous temperature monitoring of the investigational medicinal product would be logistically difficult to achieve and, from a risk perspective based on the clinical use of the medicine, in excess of current practice standards. However in an effort to balance any potential risks associated with limited exposure to temperatures outwith the recommended storage temperature of 25oC, opened tubes will be discarded after 7 days.

#### Drug accountability

In order to ensure full traceability, the batch number used for each treatment of every individual participant will be recorded on the Case Report Form. Details will also be recorded on the CRF where there is only partial application.

### Pharmacovigilance

#### Definitions of adverse events

##### Adverse Event (AE)

Any untoward medical occurrence in a subject to whom a medicinal product has been administered, including occurrences which are not necessarily caused by or related to that product.

##### Adverse Reaction (AR)

Any untoward and unintended response in a subject to an investigational medicinal product which is related to any dose administered to that subject.

#### Serious Adverse Event (SAE) or Serious Adverse Reaction (SAR)

Any adverse event or adverse reaction that:results in death,is life threatening,requires hospitalisation or prolongation of existing hospitalisation,results in persistent or significant disability or incapacity,consists of a congenital anomaly or birth defect,is otherwise considered medically significant by the investigator,Important adverse events/reactions that are not immediately life-threatening or do not result in death or hospitalisation but may jeopardise the subject or may require intervention to prevent one of the other outcomes listed in the definition above.

### Suspected Serious Adverse Reaction (SSAR)

Any adverse reaction that is classed in nature as serious and which is consistent with the information about the medicinal product in question set out in the summary of product characteristics (SmPC) or the Investigator’s Brochure (IB).

#### Suspected Unexpected Serious Adverse Reaction (SUSAR)

Any adverse reaction that is classed in nature as serious and which is not consistent with the information about the medicinal product in question set out in the SmPC or the Investigator’s Brochure (IB).

#### Detection, recording and reporting of Adverse Events

It is not proposed to collect details of all adverse events occurring in this study. Only information on adverse reactions to the IMP will be collected. The applications are spaced approximately 6 months apart, and it is inappropriate and unnecessary to attempt to collect information throughout each 6 month period on events unrelated to the varnish application, when it is known what the very specific, immediate and limited range of possible adverse reactions may be. Any adverse reaction is extremely likely to be seen within a maximum of 24 h post application. Any adverse events reported by parents during that time will be recorded and evaluated by the Childsmile coordinator and the local Principal Investigator irrespective of whether it constitutes a possible reaction or an unconnected event.

All Adverse reactions must be recorded, notified, assessed, reported, analysed and managed in accordance with the Medicines for Human Use (Clinical Trials) Regulations 2004 (as amended) and this protocol. (See Safety Flow chart- Additional file 8).

Any adverse reactions to the fluoride varnish (e.g., mucositis, allergy etc.), whether noted by Childsmile staff or reported to Childsmile staff by parents or the nursery school, will cause either the study dental nurse or dental health support worker to record details in the Case Report Form and to inform the site Principal Investigator to review such events. The parents or guardian may refer to the fluoride varnish aftercare leaflet for details of the local Childsmile Coordinators acting as the contact point regarding any possible adverse reaction.

The site Principal Investigator will assess the severity and seriousness of such events, and re-assess their relatedness to the administration of Duraphat varnish. Events deemed to be serious and related to the administration of the varnish will be classified as serious adverse reactions (SARs). SARs are to be reported by the site to the Sponsor’s Pharmacovigilance Office within 24 h of awareness of such event for assessment against the criteria of expectedness. The management of SARs is detailed below.

The expectedness of an adverse reaction is assessed against the approved Reference Safety Information i.e., the list of expected reactions detailed in the SmPC.

The following is noted in the SmPC:“In subjects with a tendency to allergic reactions, oedematous swelling of the oral mucosa has been observed in exceptional cases, especially after extensive application. If necessary, the dental suspension layer can easily be removed from the mouth by brushing and rinsing. Ulcerative gingivitis and stomatitis have been reported by sensitive individuals.In rare cases, asthma attacks may occur in participants who have bronchial asthma.In participants with gastric sensitivity, retching may exceptionally occur after a high dosage and extensive application.”

The expectedness of a SAR will be determined by the Chief Investigator following discussion with the site Principal Investigator.

#### Severity

This should be assessed and described using the following categories:mild-awareness of event but easily tolerated,moderate-discomfort enough to cause some interference with usual activity,severe-inability to carry out usual activity.

Any AE that is assessed as serious, is suspected of having a causal relationship to the trial medication and is unexpected is a SUSAR and will require expedited reporting to the MHRA/Ethics Committee as detailed below. Should an SAR be deemed to be unexpected, the Pharmacovigilance Office will liaise with the Chief Investigator to complete the expedited safety report.

Adverse reactions and Serious Adverse Reactions that occur up to 24 h after Fluoride varnish application will be reported.

Any adverse reactions present at the last application must be followed up until the event is resolved. The participant is considered to have completed the study EITHER after the completion of the last visit or contact (e.g., phone contact with the site Principal Investigator), OR after the last application of fluoride varnish, whichever is later; OR the participant can no longer comply with the requirements for any further study visits or evaluations.

#### Reporting of serious adverse reactions

All SARs (as detailed above) arising during the study will be reported by the site Principal Investigator or site Childsmile study team following review by the Principal Investigator to the sponsor (Glasgow Clinical Trials Unit (GCTU) Pharmacovigilance (PV) Office) as soon as reasonably practicable and in any event within 24 h of first becoming aware of the event. Any follow up information should also be reported.

A Serious Adverse Event form is completed and forwarded to the Pharmacovigilance Office.The GCTU Generic CTIMP SAE form is downloaded from www.glasgowctu.org, printed off, completed and signed. The form is then faxed to the Pharmacovigilance Office on [name]. A copy is placed in the Study Site File.If necessary a verbal report can be given by contacting the Pharmacovigilance Office on [name]. This must be followed up as soon as possible with a signed written report.

Serious adverse reaction details will be transferred to the Glasgow Pharmacovigilance database.

All SUSARS must be reported in an expedited fashion to the MHRA and Ethics CommitteeFatal or life threatening SUSARs: not later than 7 days after the sponsor had information that the case fulfilled the criteria for a fatal or life threatening SUSAR, and any follow up information within a further 8 days.All other SUSARs: not later than 15 days after the sponsor had information that the case fulfilled the criteria for a SUSAR

The Pharmacovigilance office will report SUSARs to the MHRA on behalf of the Chief Investigator via the MHRA eSUSAR reporting system and to Ethics committee by email.

#### Annual safety reporting

An annual safety report is required to be submitted to MHRA and REC within 60 days of the anniversary of the issue of the Clinical Trials Authorisation. The Chief Investigator will submit this report in liaison with the Pharmacovigilance Office.

### Statistics and data analysis

#### Statistical analysis plan

The study will have a comprehensive Statistical Analysis Plan, which will govern all statistical aspects of the study, and will be authored by the trial statistician and agreed by the Trial Management Group (TMG) before any unblinded data is seen.

Binary endpoints such as evidence of any new decay will be analysed by Mantel-Haenszel Chi-squared tests and odds-ratios, with the attendant 95 % confidence intervals. This type of analysis will also be carried out on safety event data. Changes in d_3_mft will be analysed by Wilcoxon tests, unless these changes are normally distributed and therefore suitable for analysis by Analysis of Covariance. Compliance will be compared with a chi-squared test. The subgroup analyses will be carried out for the primary endpoint using logistic regression with interaction terms between treatment and subgroup. All statistical tests will be two-tailed tests at the 5 % significance level. There should be no concerns regarding multiple testing. All randomised controlled trials examine secondary endpoints to examine consistency of results and to generate hypotheses for further research.

All analyses will follow the intention to treat principle [8, 11]. Study subjects will be analysed in their randomised groups regardless of the treatment actually received. Also, subjects who violate the rules of the study (‘protocol violators’) will be included in all of the analyses, provided that the 2 year endpoint data has been recorded. Ideally an intention to treat analysis would be carried out on all of the randomised subjects, but there is usually some missing primary endpoint data that prevents this. We will also carry out a ‘Worst Case Analysis’ of the Primary Endpoint. In this analysis the missing endpoints will be assumed to be treatment failures, e.g., ‘new decay’.

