#### Safety analysis

The safety data (adverse reactions) – both numbers of subjects and reactions – will be summarised by randomised group and overall using descriptive statistics. No formal statistical tests comparing the randomised groups will be pre-specified.

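### The protocol pre-specifies Mantel-Haenszel tests on safety events in one section and disclaims pre-specified safety tests in another, and the ordered test would not be interpretable

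*Protocol article*

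**What the plan says.** The protocol article deals with safety analysis in two places.

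- **Statistical analysis plan section.** "Binary endpoints such as evidence of any new decay will be analysed by Mantel-Haenszel Chi-squared tests and odds-ratios, with the attendant 95 % confidence intervals". The next sentence extends this to safety: "This type of analysis will also be carried out on safety event data". The same paragraph fixes the error rate: "All statistical tests will be two-tailed tests at the 5 % significance level".
- **Safety analysis section.** The safety data are identified as adverse reactions, counted both as subjects and as reactions. They "will be summarised by randomised group and overall using descriptive statistics", and "No formal statistical tests comparing the randomised groups will be pre-specified".

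Four other sections determine what those data can contain.

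- **Detection, recording and reporting of Adverse Events:** "Only information on adverse reactions to the IMP will be collected". Reactions are expected within 24 h of an application, and there is one wider provision for that period: "Any adverse events reported by parents during that time will be recorded and evaluated by the Childsmile coordinator and the local Principal Investigator", whether or not the event is thought to be connected.
- **Adverse Reaction (AR):** the definition given is "Any untoward and unintended response in a subject to an investigational medicinal product which is related to any dose administered to that subject".
- **Severity:** reporting of reactions, serious or not, covers the 24 h after varnish is applied.
- **Visit 1/visit 2:** control children are brushed with an applicator that carries no varnish.

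**The concern.** There are two problems, and the second makes the first matter.

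1. **Contradiction.** Naming a test, an effect measure, a confidence level and a significance level for safety events is pre-specification. The Safety analysis section says that no between-group test will be pre-specified. Whoever writes the full analysis plan cannot comply with both. If the conflict stays open, the choice between testing and describing could be made after the counts are known.

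2. **Unsuitable test.** The outcome depends on receiving varnish, through both its definition and its reporting window. Only one arm receives varnish in the study. A between-arm test then compares children who can readily have the event recorded with children who mostly cannot. A p-value on either side of 0.05 could be misread as evidence for or against harm.

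**Working it through.** **Plan's own figures.** No safety figure is stated, so there is none to reproduce. The group size used below comes from the Sample size section and does reproduce. A two-sided 5% chi-squared test with 90% power for 0.41 against 0.31 needs 483 per group (power at 483 = 0.9005). Allowing for 40% dropout, 483 / (1 - 0.40) = 805 per group.

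**Can both sections be obeyed?**

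| | Statistical analysis plan | Safety analysis |
|---|---|---|
| Data | safety event data | safety data, i.e. adverse reactions |
| Method | Mantel-Haenszel chi-squared, odds ratio, 95% CI | descriptive statistics by group and overall |
| Between-group test | ordered, two-sided 5% | none pre-specified |

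The last row is a direct conflict.

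**What would the ordered test do?** Let *a* be the number of varnish-arm children with a reaction, with none in the control arm, *n* = 805 per arm and *N* = 1,610. The Mantel-Haenszel chi-squared in a single stratum is

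(N - 1)(ad - bc)² / [(a+b)(c+d)(a+c)(b+d)], with b = n - a, c = 0, d = n.

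This reduces to (N - 1)a / (N - a), which depends only on the varnish-arm count once the group size is fixed.

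| Reactions, varnish vs control | Chi-squared | Mantel-Haenszel p | Fisher exact p | Odds ratio |
|---|---|---|---|---|
| 3 vs 0 | 1609 × 3 / 1607 = 3.004 | 0.083 | 0.25 | infinite |
| 4 vs 0 | 1609 × 4 / 1606 = 4.007 | 0.045 | 0.12 | infinite |
| 5 vs 0 | 1609 × 5 / 1605 = 5.012 | 0.025 | 0.062 | infinite |

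With 0 vs 0 the odds ratio is undefined. At 483 per arm the Mantel-Haenszel p-values are the same to three decimals (0.083, 0.045, 0.025). The Fisher column is only for comparison: at 4 and 5 reactions it gives the opposite reading from the test the protocol orders.

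**How likely are four or more reactions?** The article gives no expected rate of reactions, so a range is assumed. With 805 children and a true risk per child of 0.1%, 0.2%, 0.5% or 1%, the binomial probability of at least four affected children is 0.009, 0.080, 0.572 or 0.960. Within that range the ordered test goes from almost never significant to almost always significant. The control arm adds almost no information about background events in any of these cases.

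**The case against.** The strongest objection is to reading the control count as zero by definition and the test as therefore meaningless. A reader might infer this from the adverse reaction definition and the sham brush, but the article does not support it fully.

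- The Rationale for chosen treatment schedule section allows children varnish from their own dentist up to twice a year and does not limit this to one arm.
- Parent-reported events within the 24 h window are recorded even if unconnected.
- Children are analysed as randomised, so a control child given varnish in error still counts as a control.
- A suspected reaction could be reported after a sham contact and only later judged unrelated.

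This stands: a few control events are possible. It does not restore a fair comparison, because the window runs from a varnish application and the article does not provide for the same recording after sham contacts.

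Three further objections also stand.

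- The Safety analysis section says tests will not be pre-specified. That is weaker than saying none will be done. The conflict remains, because the other section does pre-specify one.
- The plan should not be faulted for omitting per-application rates or exact limits. It already summarises subjects and reactions, records the batch at each treatment, and may leave presentation to the full analysis plan.
- The Safety analysis section is the dedicated one, and a sensible analyst might follow it. That lowers the stakes but does not remove the contradiction.

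**Conclusion.** The point holds as a minor one. The two sections give incompatible instructions for the same data, and this is visible in the article without the full analysis plan. The instruction to test is the weaker of the two, because unequal ascertainment leaves the control count at or near zero and the p-value mainly reflects the varnish-arm count. In the illustration, the conventional threshold is crossed between three reactions (p = 0.083) and four (p = 0.045).

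Those figures assume 805 children per arm, no control reactions and a single stratum. The article does not name strata for the Mantel-Haenszel test. The reaction counts are illustrative, not predicted. The stronger claim that a control reaction is impossible is not supported and is not needed. Nothing here touches the primary analysis, the sample size or the efficacy conclusions.

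**What to change.** In the Statistical analysis plan section, delete the sentence "This type of analysis will also be carried out on safety event data" and let the descriptive rule in the Safety analysis section stand alone. This costs one deleted sentence, before any unblinded data are seen.

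Optionally, add one line to the full analysis plan: report reactions per treated child and per application actually delivered, with exact 95% confidence intervals. For scale, no reactions in all 805 × 4 = 3,220 planned applications would give a one-sided 95% upper limit of about 3 / 3,220 = 0.093% per application (two-sided exact limit about 0.11%). Missed visits and dropout will shrink that denominator and widen the limit.

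If a between-arm comparison is wanted, events would have to be collected in the same way and over the same period after varnish and sham contacts. The article does not currently provide for this. It would be a change to data collection and would cost more than an edit to the wording.
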